#### Primary outcome

The primary outcome will be the decannulation success rate following the 3-week intervention. Successful decannulation will be defined as the absence of reintubation within 72 h following tracheostomy tube removal. The decannulation process will adhere to a strictly standardised protocol, with specific criteria as follows: minimal secretions with effective clearance; good cough function (peak cough flow >160 L/min); absence of hypoxaemia (SpO2 ≥ 92%), respiratory distress, or reduced level of consciousness during a 24 h continuous tracheostomy tube occlusion test; and normal swallowing function. The decannulation success rate will be calculated as the proportion of successful decannulation relative to the total number of cases treated and expressed as a percentage. This outcome will be assessed at the end of the 3-week intervention.

Decannulation failure will be defined as the occurrence of any of the following conditions within 72 h post-decannulation: severe respiratory distress (respiratory rate >35 breaths/min); persistent hypoxaemia (requiring FiO2 > 0.5 to maintain SpO2 ≥ 90%); hypercapnia (PaCO2 > 50 mmHg and pH < 7.30); or clinical need for reintubation.

To ensure objectivity and accuracy, decannulation decisions will be made jointly by at least two therapists and rehabilitation physicians who are blinded to patient group allocation. This double-blind assessment design minimizes bias and enhances the reliability of study outcomes.

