Clinical outcome indicators will include the length of hospital stay, the incidence of respiratory-related complications, and the rate of reintubation within 72 h following decannulation. Relevant data will be extracted from patients’ electronic medical records. Length of stay will be defined as the total number of days from study enrollment to hospital discharge. Respiratory-related complications will be defined to include common conditions such as pneumonia, atelectasis, and pneumothorax. All clinical outcome indicators will be recorded by a designated study physician.

Quality of life will be evaluated using three instruments: the EQ-5D-5L Health-Related Quality of Life Questionnaire, the Breathing Difficulty Assessment (Borg Scale), and the Hospital Anxiety and Depression Scale (HADS). The EQ-5D-5L assesses five dimensions of health status—mobility, self-care, usual activities, pain/discomfort, and anxiety/depression—each rated on five levels. It also includes a visual analogue scale (VAS) ranging from 0 to 100 to evaluate the patient’s overall health status. Dyspnoea will be measured using the Revised Borg Scale (0–10 points), administered at rest and following standardized activities (e.g., sit-to-stand test), to reflect exertional breathlessness during daily tasks. The Hospital Anxiety and Depression Scale (HADS) comprises 14 items divided into two subscales—anxiety and depression—each containing seven items to evaluate corresponding symptoms. For patients unable to complete the questionnaires independently, assistance will be provided by trained research personnel to ensure accuracy and completeness. Assessments will be conducted at baseline (pre-intervention), upon completion of the 3 week intervention, and at 3 months post-intervention.

In the present study, a respiratory therapist will assess each patient’s readiness for decannulation daily and will document the decannulation attempt process and its outcome in detail. Post-decannulation follow-up will include relevant assessments within 72 h and a clinic or telephone visit during the first week. All assessments will be conducted by healthcare professionals blinded to group assignments. Ultrasound measurements will be obtained by trained physicians using a standardised protocol; respiratory parameters will be measured by qualified respiratory therapists; and quality of life will be assessed by study nurses.

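### The primary endpoint has two conflicting rules, so a patient who is not reintubated can be both a success and a failure, and no cut-off says which tube removals count

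*Protocol article*

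**What the plan says.** All of the following is in the protocol article.

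- **Success (Primary outcome):** "Successful decannulation will be defined as the absence of reintubation within 72 h following tracheostomy tube removal". Reintubation is the only event that disqualifies a patient.
- **Failure (Primary outcome, following paragraph):** "Decannulation failure will be defined as the occurrence of any of the following conditions within 72 h post-decannulation". The list opens with "severe respiratory distress (respiratory rate >35 breaths/min", continues with persistent hypoxaemia and with hypercapnia, each given a numerical threshold, and ends with "or clinical need for reintubation".
- **Rate (Primary outcome):** it is "the proportion of successful decannulation relative to the total number of cases treated".
- **Time of reading (Primary outcome):** "This outcome will be assessed at the end of the 3-week intervention".
- **Schedule (Table 1):** the decannulation outcome, listed under the primary outcome, is ticked at V4 (week 3), V5 (72 h after decannulation, ±2 h), V6 (one week after decannulation) and V7 (three months).
- **When tubes come out (Secondary outcomes):** a respiratory therapist will assess each patient's "readiness for decannulation daily and will document the decannulation attempt process". Removal can therefore fall on any day, including the last days of week 3.

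**The concern.** The trial has one primary endpoint and 60 patients. The two definitions cover the same 72 h but do not divide decannulated patients into two separate groups. One rests on an event (reintubation). The other rests on physiological states, or on a need, that can occur without that event. No sentence says which prevails, so two analysts following the text faithfully could report different success counts from the same data.

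The timing has a related gap. The text places the reading at the end of week 3, but the definition needs 72 h of observation after removal, and Table 1 spreads the same outcome over four visits. Nothing states the last removal day that counts towards the three-week endpoint.

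This is a conflict between stated rules, not detail that could be left to an analysis plan. It also reaches back to planning: the Sample size calculation section does not say which rule classified the pilot successes (6 of 12 and 10 of 12) on which the 50% and 80% assumptions partly rest.

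**Working it through.** **Step 1. Apply both definitions to each type of patient.**

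| Course | Success rule | Failure rule | Result |
|---|---|---|---|
| Decannulated, no listed condition, not reintubated | yes | no | clear |
| Decannulated, reintubated within 72 h because clinically needed | no | yes | clear |
| Decannulated, distress, hypoxaemia or hypercapnia criterion met, not reintubated | yes | yes | contradiction |
| Decannulated, reintubation judged necessary but not done | yes | yes | contradiction |
| Never decannulated | no | no | neither label, but a non-success, because the denominator is all cases treated |

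**Step 2. Apply the stated reading time.**

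- Tube removed more than 72 h before the end of week 3: the window has closed by V4, so there is no problem.
- Tube removed in the last 72 h of week 3: the window is still open at V4 and closes at V5.
- Tube removed after week 3: Table 1 would record it, and no rule says whether it counts.

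**Step 3. Illustrate what reclassification could do.** The plan gives no figure for this and no frequency for the failure conditions, so the shifts below are assumptions. Inputs: 30 per arm and the planned rates of 80% and 50% (Sample size calculation), that is 24/30 and 15/30. Test: uncorrected chi-square on one degree of freedom, with two-sided Fisher beside it because the Statistical analysis section allows either.

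χ² = (p₁ − p₂)² / [p̄(1 − p̄)(2/30)]. For 24 vs 15: p̄ = 39/60 = 0.65, so χ² = 0.09 / (0.65 × 0.35 × 0.0667) = 5.93.

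| TFRL-IMT vs control | Change | χ² | Chi-square p | Fisher p |
|---|---|---|---|---|
| 24/30 vs 15/30 | none | 5.93 | 0.015 | 0.029 |
| 23/30 vs 15/30 | one, TFRL-IMT only | 4.59 | 0.032 | 0.060 |
| 22/30 vs 15/30 | two, TFRL-IMT only | 3.45 | 0.063 | 0.110 |
| 23/30 vs 14/30 | one in each arm | 5.71 | 0.017 | 0.033 |
| 22/30 vs 13/30 | two in each arm | 5.55 | 0.018 | 0.035 |

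**Step 4. Illustrate the effect on power if the failure list prevails.** Assume a share r of patients who are not reintubated meets a listed condition, equally in both arms. The rates become 0.5(1 − r) and 0.8(1 − r). With n = 30 per arm and two-sided α = 0.05,

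power = Φ{[|p₁ − p₂|√n − 1.96√(2p̄(1 − p̄))] / √(p₁(1 − p₁) + p₂(1 − p₂))}.

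For r = 0: (0.3 × 5.477 − 1.96 × 0.6745) / 0.6403 = 0.50, so power is 69%.

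| r | Rates | Power at 30 per arm |
|---|---|---|
| 0 | 50% / 80% | 69% |
| 5% | 47.5% / 76% | 63% |
| 10% | 45% / 72% | 57% |
| 20% | 40% / 64% | 46% |

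The starting value is 69%, not the planned 80%, because the plan's 26 per group does not follow from its stated inputs. That is a separate matter and plays no part in this point.

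**The case against.** The overlap between the definitions cannot be argued away, but several stronger readings can.

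- **Patients never decannulated are unclassifiable.** A reader might infer this because they meet neither label. The stated denominator settles it: they are in the denominator and not in the numerator. Explicit coding is still worth a sentence, because cases treated need not equal all randomised patients under intention to treat.
- **The endpoint is always read too early.** This too goes beyond the text. It applies only to removals in the last 72 h of week 3, and Table 1 already schedules V5 at the right moment. For those patients the reading is delayed by up to three days, not lost. The article gives no distribution of removal days, so their number cannot be stated. The section also ties the outcome to the three-week intervention, which argues against counting a removal at month three, although no cut-off is written.
- **Unblinded providers will classify borderline cases by arm.** The article says the opposite about who decides. Outcome assessors are blinded (Randomisation and blinding), decannulation decisions are made jointly by blinded staff (Primary outcome), and the assessments are made by blinded professionals (Secondary outcomes). The ambiguity remains under perfect blinding, but it is not evidence of bias.
- **Two patients overturn the result.** This holds only if both are in the TFRL-IMT arm. Nothing in the article suggests that these events fall in one arm, and equal shifts leave p almost unchanged.

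**Conclusion.** The point stands in two parts. First, the success and failure definitions contradict each other for any decannulated patient who meets a listed failure condition, or is judged to need reintubation, without being reintubated. No precedence is stated. Second, the end-of-week-3 reading and the Table 1 visits are not reconciled, and no removal cut-off is given.

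The size is unknown, because the article gives no frequency for the failure conditions and no distribution of removal days. On the planned counts, the effect ranges from negligible (two reclassified in each arm, p = 0.018) to a change of conclusion (two in the TFRL-IMT arm alone, p = 0.063; by Fisher's test one is enough, p = 0.060). These shifts are illustrations, not predictions. The point does not rest on them: a sole primary endpoint that can label one patient both ways is wrong as written and needs correcting before unblinding.

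**What to change.** Before unblinding, amend the Primary outcome section, Table 1 and the analysis plan as follows.

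1. Reconcile the two definitions into one binary rule with stated precedence, applied identically in both arms. Which criteria count is for the investigators to decide.
2. State the last day of tube removal that counts towards the three-week endpoint.
3. Read the outcome 72 h after removal, at V5, instead of at V4.
4. Count every other randomised patient as not a success, including those never decannulated and those first decannulated after the cut-off.
5. Label decannulation status at V6 and V7 as secondary.
6. Confirm that the 50% and 80% planning rates, and the pilot counts behind them, refer to the chosen rule.

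The cost is mainly wording, since the V5 visit is already scheduled. If the hypercapnia criterion is kept, the team should check that the blood-gas data it needs will be available, because Table 1 does not list them separately. The downside is that keeping the broader failure list may lower both success rates and hence power, by an amount that depends on event frequencies the article does not give.

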#### Secondary outcomes

Secondary outcomes will include diaphragmatic function, respiratory parameters, clinical outcomes, and quality of life.

Diaphragm function will be evaluated using a portable ultrasound device (SII, Sonosound Medical Devices Co., Ltd.). Diaphragm excursion will be measured using M-mode ultrasound. Patients will be positioned semi-recumbently, and a trained sonographer will use a convex-array probe placed at the mid-axillary line beneath the right costal margin to obtain the maximal diaphragm excursion during quiet breathing. Each measurement will be repeated three times and averaged. Diaphragm thickness will be measured with B-mode ultrasound using a high-frequency linear-array probe placed along the anterior axillary line at the 8th to 9th intercostal space, the thickness will be assessed at end-expiration and end-inspiration. All measurements will be performed at baseline (pre-intervention) and after 3 weeks of intervention.

Respiratory parameters, including MIP, forced vital capacity (FVC), peak expiratory flow (PEF), and forced expiratory volume in one second (FEV1), will be assessed using a portable spirometer (X1, Seck Medical Devices Co., Ltd., Xiamen, China). The tracheostomy cuff is inflated to 25 cmH₂O with patients in a semi-recumbent position (45°). For MIP assessment, patients will perform five maximal inspiratory efforts from end-expiratory volume, with the highest value being recorded from three reproducible trials, each demonstrating <10% variation. For spirometric parameters (FVC/PEF/FEV1), patients will perform three forced expiratory maneuvers from total lung capacity with ≥30 s rests between trials, adhering to ATS/ERS standards. Specifically, FVC will use the highest value from ≥2 reproducible trials (<5% variation), PEF will take the highest peak flow from any valid trial, and FEV1 will use the highest value from ≥2 trials with acceptable start-of-test criteria. All measurements will be performed at baseline (pre-intervention) and after 3 weeks of intervention.

Clinical outcome indicators will include the length of hospital stay, the incidence of respiratory-related complications, and the rate of reintubation within 72 h following decannulation. Relevant data will be extracted from patients’ electronic medical records. Length of stay will be defined as the total number of days from study enrollment to hospital discharge. Respiratory-related complications will be defined to include common conditions such as pneumonia, atelectasis, and pneumothorax. All clinical outcome indicators will be recorded by a designated study physician.

Quality of life will be evaluated using three instruments: the EQ-5D-5L Health-Related Quality of Life Questionnaire, the Breathing Difficulty Assessment (Borg Scale), and the Hospital Anxiety and Depression Scale (HADS). The EQ-5D-5L assesses five dimensions of health status—mobility, self-care, usual activities, pain/discomfort, and anxiety/depression—each rated on five levels. It also includes a visual analogue scale (VAS) ranging from 0 to 100 to evaluate the patient’s overall health status. Dyspnoea will be measured using the Revised Borg Scale (0–10 points), administered at rest and following standardized activities (e.g., sit-to-stand test), to reflect exertional breathlessness during daily tasks. The Hospital Anxiety and Depression Scale (HADS) comprises 14 items divided into two subscales—anxiety and depression—each containing seven items to evaluate corresponding symptoms. For patients unable to complete the questionnaires independently, assistance will be provided by trained research personnel to ensure accuracy and completeness. Assessments will be conducted at baseline (pre-intervention), upon completion of the 3 week intervention, and at 3 months post-intervention.

In the present study, a respiratory therapist will assess each patient’s readiness for decannulation daily and will document the decannulation attempt process and its outcome in detail. Post-decannulation follow-up will include relevant assessments within 72 h and a clinic or telephone visit during the first week. All assessments will be conducted by healthcare professionals blinded to group assignments. Ultrasound measurements will be obtained by trained physicians using a standardised protocol; respiratory parameters will be measured by qualified respiratory therapists; and quality of life will be assessed by study nurses.

Data will be collected at the following time points: baseline within 24 h prior to the intervention, and final assessment at the conclusion of the 3 week intervention period. Additionally, follow-up will be conducted in the clinic or via telephone 3 months after the intervention. Any adverse events observed during the evaluations, including discomfort during respiratory measurements or abnormalities in ultrasound examinations, will be recorded in detail. To minimize bias, all follow-up assessments will be conducted by trained assessors blinded to group allocation. For patients lost to follow-up, the study team will make proactive attempts to contact them via phone or text to collect outcome data. If contact cannot be established after three consecutive attempts, the patient will be classified as lost to follow-up.

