### Intervention protocol

#### Experimental group interventions

In this study, patients in the experimental group will receive TFRL-IMT in addition to conventional treatment. TFRL-IMT will be administered using the inspiratory muscle training module of a portable pulmonary function testing device (X1, Seck Medical Devices Co., Ltd., Xiamen, China). The initial training load will be set at 30% of the subject’s MIP, which will be measured using the device’s built-in function. During the study period, MIP will be measured weekly, and the training load will be adjusted to 30% of the current MIP. Additionally, resistance will be gradually increased by 5% per week until 60% of MIP is reached and maintained, depending on the patient’s tolerance.

The training programme will last for 3 weeks, during which patients will undergo two sessions per day, each comprising five sets of six maximal inspiratory efforts with a one-minute rest between sets. During each session, the patient’s tracheal cannula will be connected to the device valve via a specialized connecting tube, and the patient will be instructed to inhale as forcefully and rapidly as possible, followed by slow exhalation. All training will be conducted under the supervision of healthcare professionals to ensure training quality and patient safety. The rehabilitation therapist will document the actual load, completion status, and any adverse events during each training session.

In patients with concurrent respiratory infections, appropriate antibiotics will be administered based on clinical manifestations and sputum culture results. In patients with thick sputum, nebulized salbutamol (2.5 mg) combined with ipratropium bromide (0.5 mg) will be administered three times daily at 8:00 a.m., 12:00 p.m., and 8:00 p.m.

To evaluate the efficacy and safety of the intervention, MIP values will be measured before and after training using the same portable pulmonary function device. Simultaneously, vital signs such as including heart rate, blood pressure, respiratory rate, and oxygen saturation will be continuously monitored.

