#### Outcome measures

The timetable for enrolment, intervention, and assessment is presented in Table 1.

**Table 1 tab1:** SPIRIT schedule of enrollment, interventions and assessment.

Study phase	Screening	Baseline	Intervention period			Follow-up period		
Visit	V0	V1	V2	V3	V4	V5	V6	V7
Time window	−7d ~ 0d	−24 h	Week 1	Week 2	Week 3	±2 h	±1d	±7d
Basic information								
Informed consent	√							
Demographics	√							
Medical history	√							
Inclusion/exclusion	√							
Primary outcome								
Decannulation readiness^a^			√	√	√			
Decannulation outcome					√	√	√	√
Secondary outcomes								
Diaphragm function^b^		√			√			
Respiratory parameters^c^		√			√			
Clinical outcomes^d^					√	√	√	√
Quality of life assessment^e^		√			√			√
Safety assessment								
Adverse events		√	√	√	√	√	√	√

V0 (screening): within 7 days before enrollment; V1 (baseline): within 24 h pre-intervention; V2-V4 (intervention period): ±1 day; V5 (post-decannulation 72 h): ±2 h; V6 (post-decannulation 1 week): ±1 days; V7 (3 months follow-up): ±7 days.

a Decannulation preparation assessment will include: The amount of secretion is small and the patient is able to clear it effectively; Effective cough with a peak cough flow rate >160 L/min; no hypoxaemia (SpO₂ ≥ 92%), respiratory distress, or decrease in the level of consciousness during the 24 h consecutive tracheostomy tube occlusion test; Swallowing function is normal.

b Diaphragmatic function assessment will include: diaphragmatic mobility and diaphragmatic thickness.

c Respiratory function parameters include: MIP, FVC, PEF, FEV1.

d Clinical outcome evaluation will include: length of hospital stay, rate of respiratory-related complications, and rate of reintubation within 72 h of decannulation.

e Quality of life assessment includes: EQ-5D-5L Health-Related Quality of Life Questionnaire, The Breathing Difficulty Assessment (Borg Scale), and The Hospital Anxiety and Depression Scale (HADS).

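### Diaphragm excursion is read only in quiet breathing, although the training consists of maximal inspiratory efforts

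*Protocol article*

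**What the plan says.** Under Secondary outcomes, the protocol article sets two ultrasound measures of diaphragm function, both taken at baseline and after three weeks.

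- **Excursion (M-mode).** A "convex-array probe placed at the mid-axillary line beneath the right costal margin" is used to "obtain the maximal diaphragm excursion during quiet breathing". Then: "Each measurement will be repeated three times and averaged".
- **Thickness (B-mode).** A "high-frequency linear-array probe placed along the anterior axillary line at the 8th to 9th intercostal space" is used, and "the thickness will be assessed at end-expiration and end-inspiration". The article does not give the depth of breath, the side, or a variable derived from the two readings.

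Footnote b of Table 1 names the outcome variables: "Diaphragmatic function assessment will include: diaphragmatic mobility and diaphragmatic thickness".

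Under Experimental group interventions, each session is "five sets of six maximal inspiratory efforts with a one-minute rest between sets", with the patient "instructed to inhale as forcefully and rapidly as possible, followed by slow exhalation". The resistance is set as a share of MIP, but the effort asked of the patient is maximal.

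**The concern.** Quiet breathing produces a tidal excursion, whose size follows ventilatory demand at rest. It does not show how far the diaphragm can move when the patient tries hard. A diaphragm that has become stronger need not travel further in a resting breath. If training changes what the muscle can do under effort, a resting reading is poorly placed to show it.

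The wording adds a practical problem. *Maximal* and *quiet breathing* point in different directions, and the following sentence asks for an average. One sonographer could take the largest of several tidal breaths and another the mean of three ordinary ones.

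At stake is what a null ultrasound result would mean. The Discussion offers improved diaphragm function as one route to better ventilation and cough. If excursion does not differ between groups, the reader could not tell an absent effect on diaphragm movement from one that was not examined under effort.

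**Working it through.** The plan states no figure for this outcome, so there is nothing to reproduce. The check sets the passages side by side and then bounds one related issue, the side scanned.

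**Effort level, measure by measure**

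| Item | Effort stated | Diaphragm-specific? |
|---|---|---|
| Training | maximal inspiration | – |
| MIP | maximal: five efforts, with a <10% reproducibility rule | no, global |
| Excursion | quiet breathing | yes |
| Thickness | respiratory phases given, breath depth not stated | yes |

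The plan thus specifies a maximal manoeuvre with care for MIP. Neither diaphragm-specific measure is stated to use one, and for excursion the text sets the opposite. That part is written text, so it does not depend on what a fuller protocol might add. Feasibility is not the obstacle: patients must be able to follow simple commands to enter, and they already perform maximal efforts for MIP at baseline and week 3.

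**Thickness**

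The two readings are sufficient for a thickening fraction:

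TF = (end-inspiratory − end-expiratory) / end-expiratory thickness.

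No new data are needed. The fraction is comparable between visits only if the inspiratory effort is the same at both.

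**Side scanned (illustration)**

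Excursion is read on the right in everyone. Lesion side is not an entry limit, a listed baseline descriptor or a stratification factor. Suppose, purely as an assumption, that a share q of patients have a weaker right side, and that it differs from an unaffected right side by g within-side SDs. For a comparison of raw week-3 values at two-sided 5% and 80% power:

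- detectable difference = (1.960 + 0.842) × √(2/n) × √(1 + q(1−q)g²), in within-side SD units;
- n = 26 or 30 per arm, from Sample size calculation, used here only as head counts;
- q = 0.3 to 0.5 and g = 0, 0.5 or 1.0 are assumed.

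| n per arm | g = 0 | g = 0.5 | g = 1.0 |
|---|---|---|---|
| 26 | 0.777 | 0.797–0.801 | 0.855–0.869 |
| 30 | 0.723 | 0.742–0.746 | 0.796–0.809 |

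Worked case (n = 26, q = 0.5, g = 1): 2.802 × √(2/26) × √1.25 = 0.777 × 1.118 = 0.869. The equivalent sample-size inflation is 1 + q(1−q)g², that is 1.05 to 1.06 at g = 0.5 and 1.21 to 1.25 at g = 1. These are upper values: the same side is scanned twice, so a stable side difference largely drops out once the baseline reading is used.

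**The case against.** **In defence of the plan.** Tidal excursion is a legitimate choice. It needs no cooperation, and a maximal breath may be hard to reproduce in some patients. *Maximal* can be read as the peak-to-trough amplitude of the resting trace. Inspiratory strength at maximal effort is measured anyway, through MIP at the same two visits. The article also says that ultrasound follows a standardised protocol, which is not shown.

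Much of this stands. Quiet-breathing excursion is worth keeping, and the amplitude reading is possible. But an unseen protocol cannot be assumed to undo a breathing condition that the article states outright, and MIP cannot attribute a gain to the diaphragm.

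**Stronger readings that a reader might infer, and that the document does not support:**

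- *Thickness is recorded only as an absolute value.* It is read at both phases, so thickening can be derived. Its definition, the breath depth and the side may be in the full protocol or the analysis plan.
- *The trained capacity goes unmeasured.* MIP measures it globally.
- *Paretic and unaffected hemidiaphragms are mixed, with variance that this sample cannot bear.* The document nowhere mentions hemidiaphragm weakness. If it exists, randomisation prevents bias and the precision cost is modest, as shown above. Right-sided scanning is stated for excursion only.
- *A thickening fraction is far more sensitive than thickness.* With end-expiratory thickness unchanged, it is a linear rescaling of end-inspiratory thickness. A larger percentage change is then a denominator effect, and sensitivity depends on SDs that the document does not give.

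**Conclusion.** The point holds in a narrow form. Excursion is fixed at quiet breathing, in wording that is internally inconsistent, while the intervention trains maximal inspirations. The diaphragm-specific mobility outcome is therefore not taken at the effort level the training targets. This weakens what the ultrasound can say about mechanism. It does not make the outcome invalid or leave inspiratory strength unassessed.

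How much sensitivity is lost cannot be computed from the document. The judgement rests on the premise that resting excursion follows ventilatory demand more than muscle capacity. The issue of side is secondary: at most about 0.78 to 0.87 SD in detectable difference at 26 per arm, under assumed side differences up to 1 SD, and less with baseline adjustment.

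Importance is low. It concerns one secondary outcome domain and has no bearing on the decannulation outcome, its test or the sample size. It is worth acting on because the change is small.

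**What to change.** 1. At the existing baseline (V1) and week-3 (V4) scans, add excursion during a maximal deep inspiration, with three readings, and name it the main mobility outcome. Keep quiet-breathing excursion alongside it.
2. Reword the excursion sentence so that each reading has one stated breathing condition and one summary rule.
3. Report the thickening fraction from the thickness values already planned, with end-inspiration read at the same stated effort at both visits.
4. Optionally, record lesion side from the CT or MRI already required for entry, allowing a category for bilateral or brainstem strokes where side is undefined. Analyse excursion adjusted for its baseline value.

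**Cost.** Item 1 adds a few breaths to a scheduled scan, item 2 is editorial, item 3 is a calculation, and item 4 is one data field and a covariate.

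**Downsides.** Some patients may not manage a reproducible deep breath, so failed attempts should be recorded. The stated trial period began in March 2025, so patients already enrolled may lack a deep-breath baseline. Make the change as a dated amendment before any comparison by group, and state how those patients enter the analysis.
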